##### **5.1.1 Principal Investigator**

The principal investigator has a personal responsibility to closely monitor trial subjects and an inherent authority to take whatever measures necessary to insure their safety. The principal investigator has the authority to terminate, suspend or require changes to a clinical trial for safety concerns and may delay an individual's study vaccine administration or pause study

vaccine administration in the whole trial if the investigator has some suspicion that the study vaccine might place a subject at significant risk. The principal investigator determines severity and causality with respect to the study vaccine for each adverse event. For blinded studies the principal investigator is blinded, in which case the study vaccine may consist of either a placebo, an active control, or the investigational product.

#### **5.1.1.1 Study Vaccine Pausing Rules for the Principal Investigator**

If the principal investigator determines that a suspected unexpected serious adverse reaction (SUSAR) OR a serious adverse event OR an adverse event pattern of concern that is judged to be POSSIBLY, PROBABLY or DEFINITELY related to study vaccine has occurred, the principal investigator will pause administration of study vaccine in the trial. If the principal investigator pauses study vaccine administration he or she will record this in a memorandum to the study file and notify the sponsor.

If the principal investigator pauses study vaccine administration in a trial under the rules in this section and additional clinical information becomes available that reduces the principal investigator's assessment of causality, severity or toxicity grade such that the adverse event's causality, severity or toxicity grade no longer requires pausing then the principal investigator, with the agreement of the local medical monitor, may resume study vaccine administration with a memorandum to the study file and notification of the sponsor.

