##### **5.1.3.1 Study Vaccine Pausing Rules for the Local Medical Monitor**

If the local medical monitor determines that a SUSAR OR a serious adverse event OR an adverse event pattern of concern that is judged to be POSSIBLY, PROBABLY or DEFINITELY related to study vaccine has occurred, the local medical monitor will pause administration of study vaccine in the trial. If the local medical monitor independently pauses administration of study vaccine in the study, he or she will record this in a memorandum to the study file and notify the principal investigator and sponsor who will then convene the SMC. In all cases administration of study vaccine may resume only if permitted by the SMC.

Any changes to the protocol required by the SMC as a condition of study vaccine resumption must be approved by, or submitted to, the institutional review board/ethical committee and the national regulatory authority.

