##### **5.1.4.1 Study Vaccine Pausing Rules for the Global Medical Monitor**

Since the global medical monitor is unblinded and reviews data from all Aeras trials, he or she may become aware of an adverse event pattern of concern not appreciated by the principal investigator or local medical monitor. If the global medical monitor independently determines that an adverse event pattern of concern that is judged to be POSSIBLY, PROBABLY or DEFINITELY related to study vaccine has occurred, the global medical monitor will pause administration of study vaccine in the trial. If the global medical monitor pauses administration of study vaccine in the trial he or she will record this in a memorandum to the study file and notify the local medical monitor, principal investigator and sponsor who will convene the SMC. In all cases administration of study vaccine may resume only if permitted by the SMC. Any changes to the protocol required by the SMC as a condition of study vaccine resumption must be approved by, or submitted to, the institutional review board/ethical committee and the national regulatory authority.

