#### **5.1.5 Safety Monitoring Committee**

If study vaccine administration is paused by the principal investigator, the local medical monitor, or the global medical monitor, an SMC will be convened. The SMC is composed of five voting members (two licensed physicians from South Africa, one licensed physician from the United Kingdom, and two licensed physicians from the US) and may have up to two alternate physician members. The voting members can not be directly involved with the conduct of the study, can not be employees of Aeras and must be experienced in the evaluation of adverse events in clinical trials. The SMC will also have a non-voting statistician and a non-voting Aeras member who will record committee actions.

The SMC will convene to review safety data when the last subject in the Safety Cohort (Study Group 1) completes Study Day 84. The SMC will evaluate blinded and unblinded-by-group safety data to determine if a pattern of adverse events related to MVA85A/AERAS-485 or other safety or risk concerns exist. Only the SMC and the independent statistician responsible for preparing these analyses would be unblinded during these reviews. If such a pattern

exists, the Safety Monitoring Committee will determine if additional subjects will be entered into this safety group for additional safety determination or if further studies need to be performed. The SMC will conduct a second unblinded-by-group safety and risk review after the 1000th infant completes the Study Day 84 visit. The SMC may also review an individual SAE or it may choose to review adverse events, serious adverse events, solicited adverse events, and laboratory and vital signs data. The SMC may unblind any amount of safety information needed to conduct their assessment. All procedures associated with this review, including objectives, data handling, and elements to be included for review will be documented in SMC minutes.

Based on its review and the protocol stopping rules (Section 6) the SMC will make recommendations in the SMC minutes to Aeras regarding further conduct of the study and further administration of study vaccine. The conclusions of the SMC will be communicated to the investigators and the IRB/Ethical Committees and the national regulatory authority for their information. The sponsor agrees to abide by the decision of its SMC.

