## 6 STOPPING RULES

The rules for pausing study vaccine administration by the principal investigator and local medical monitor are in Section 5.1. These rules govern the stopping of further study vaccine administration at any time during the study.

The rules for stopping further enrollment and study vaccine administration by the SMC are below:

- Death in any infant unless the SMC determines it is UNRELATED to MVA85A/AERAS-485
- An anaphylactic reaction to MVA85A/AERAS-485 in any infant
- The occurrence of a serious adverse event unless the SMC determines it is UNRELATED to MVA85A/AERAS-485.

The SMC may permit resumption of study vaccine administration if the study pause was for reasons less severe than those in the SMC stopping rules. The SMC may permit resumption of enrollment if it judges that changes to the study protocol will eliminate or greatly reduce the safety risks specified in the stopping rules. In the absence of study protocol changes, the SMC must follow the SMC study stopping rules.

If a decision to resume study enrollment and study vaccine administration is made the SMC will record their judgment in a memorandum to the study file and notify the sponsor, who will then forward the SMC memorandum to the medical monitors and principal investigators. The clinical site will be allowed to resume activities upon receipt of written notification from the sponsor. The appropriate regulatory authority will be informed in writing if the study is stopped and will be informed in writing of the decision by the SMC to resume or discontinue study activities.

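### Who may restart vaccination after an investigator pause for a related SAE or SUSAR is not settled: Section 5.1.1.1 gives a route without the SMC that Sections 5.1.5 and 6 do not acknowledge

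*Protocol*

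**What the plan says.** Section 5.1.1.1 of the protocol obliges the principal investigator to pause vaccination for a SUSAR, an SAE or an adverse event pattern of concern that is judged at least possibly related. The same section then gives a way out. It applies when "additional clinical information becomes available that reduces the principal investigator's assessment of causality, severity or toxicity grade" to the point where a pause is no longer required. With the local medical monitor's agreement, the investigator "may resume study vaccine administration with a memorandum to the study file and notification of the sponsor".

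Section 5.1.5 says: "If study vaccine administration is paused by the principal investigator, the local medical monitor, or the global medical monitor, an SMC will be convened". It makes no exception for an event that has since been downgraded.

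Section 6 begins with a referral: "The rules for pausing study vaccine administration by the principal investigator and local medical monitor are in Section 5.1". It then lists the SMC's own rules for stopping enrolment and vaccination, among them: "The occurrence of a serious adverse event unless the SMC determines it is UNRELATED to MVA85A/AERAS-485". For lesser pauses it adds: "The SMC may permit resumption of study vaccine administration if the study pause was for reasons less severe than those in the SMC stopping rules".

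For pauses imposed by the local medical monitor, Section 5.1.3.1 says: "In all cases administration of study vaccine may resume only if permitted by the SMC". Section 5.1.4.1 uses the same sentence for pauses by the global medical monitor.

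**The concern.** Safety in infants is the primary objective (Section 2.1), so the authority to restart dosing after a serious event should have one clear answer. For an investigator pause over an SAE or SUSAR, Section 5.1.1.1 describes a complete restart procedure that ends with the sponsor being told. Sections 5.1.5 and 6 bring in the SMC for the same situation.

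The bodies concerned are not equivalent. The investigator and the local medical monitor are both blinded (Sections 5.1.1 and 5.1.3). The SMC may unblind whatever safety information it needs, and its voting members may be neither sponsor employees nor directly involved in running the study (Section 5.1.5). If 5.1.1.1 is followed as written, dosing could restart before the SMC has met, on a causality judgement that Section 6 gives to the SMC.

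**Working it through.** No arithmetic applies, and the protocol gives no figure on this point to reproduce. The check is a comparison of the rules for one case: the investigator has paused for an SAE or SUSAR judged related, and new information later lowers that assessment.

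1. **Section 5.1.1.1.** The decision lies with the investigator, with the local medical monitor agreeing. The formalities are a file memorandum and notice to the sponsor. The SMC is not mentioned; it is not expressly excluded either.

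2. **What can be lowered.** The section accepts a reduction in causality, severity or toxicity grade. For an SAE the trigger is seriousness together with relatedness, and Section 5.4 treats severity and seriousness as separate concepts. A lower severity grade would therefore not by itself remove the trigger. In practice the restart would rest on causality, that is, on a judgement that the event is after all unrelated.

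3. **Section 5.1.5.** The SMC is to be convened, and investigator pauses are named. The section requires a meeting; it does not itself say that SMC permission is needed to resume.

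4. **Section 6.** The SAE rule makes the finding of unrelatedness one for the SMC. That is the same judgement that step 2 shows the investigator route relies on. Section 6 also describes the SMC as the body that may permit resumption after pauses for lesser reasons. Where the SMC decides to resume, the site waits for written notification from the sponsor. Under 5.1.1.1 the sponsor is only informed.

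5. **Does Section 6 defer to 5.1.1.1?** Its opening sentence refers to Section 5.1 for the pausing rules and says that those rules govern stopping vaccination. It is silent on resumption. Section 5.1 also contains 5.1.5, so the referral does not choose between the two routes.

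6. **Sections 5.1.3.1 and 5.1.4.1.** Of the three pausing rules, two require SMC permission to resume and one, the investigator's, does not. The permission sentences sit in the monitors' own rules and are best read as covering pauses by the monitors. They show how the protocol handles a like situation; they do not contradict 5.1.1.1.

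The result is two restart routes for one event: investigator plus local monitor under 5.1.1.1, or a convened SMC that determines relatedness or permits resumption under 5.1.5 and 6. No clause says which prevails.

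**The case against.** The strongest reply is that the design has two deliberate tiers. Short pauses are handled under 5.1 and formal stopping under Section 6. The investigator route is narrow: for an SAE or SUSAR it opens only when neither physician still sees a reason to pause. Section 5.5 lets the higher of the two causality ratings prevail, and under 5.1.3.1 a local monitor who still judges the event related must pause, which only the SMC can lift. On this view a pause whose reason has lapsed may sensibly end more simply than one that a second assessor has imposed. The absence of the SMC sentence from 5.1.1.1 alone then looks intended. Convening the SMC and resuming meanwhile can both happen.

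Much of this stands. The investigator cannot restart alone, 5.1.5 calls for convening and not permission, and 5.1.1.1 may well be meant as an exception. What does not follow is that the exception is settled. Neither 5.1.5 nor Section 6 states it, and Section 6 still gives the unrelatedness finding for an SAE to the SMC. Section 7.6 places the SMC's mandate in a charter that is not at hand and might resolve this, but the protocol's own sections should agree.

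Two stronger readings are tempting and not supported. A reader might infer from the words in 5.1.3.1, "In all cases administration of study vaccine may resume only if permitted by the SMC", that 5.1.1.1 breaks an explicit rule; that sentence concerns monitor pauses. A reader might also infer from Section 6 that every SAE halts the trial until the SMC rules. The point here does not need that reading, since it concerns only an SAE or SUSAR that has already led to an investigator pause.

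**Conclusion.** The point holds as an unreconciled safety rule, of minor severity. After an investigator pause for a related SAE or SUSAR, the protocol does not say whether two blinded physicians may restart dosing or whether the SMC must first decide. It does not show that a restart under 5.1.1.1 would be a clear breach.

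Existing provisions limit the consequence. Besides the causality and pausing rules in 5.5 and 5.1.3.1, the global medical monitor reviews all SUSAR reports (5.1.4) and can pause for a pattern that others have missed: "Since the global medical monitor is unblinded and reviews data from all Aeras trials". The sponsor informs the SMC of every SAE within three working days of learning of it (5.11).

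No number of affected infants or doses can be derived. The protocol gives neither the expected number of such pauses nor the time the SMC needs to rule. No test, estimate or power figure is affected. The conclusion assumes that Section 6's referral to 5.1 covers pausing and stopping, as its wording says, and not resumption.

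**What to change.** Add one sentence to 5.1.1.1: after a pause for a SUSAR or an SAE, vaccination may resume only with the SMC's permission. Keep the route through the investigator and local medical monitor for pauses over non-serious event patterns. State that exception by cross-reference in 5.1.5 and in the Section 6 sentence on pauses for lesser reasons.

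The cost is one sentence and two cross-references, plus a possible enrolment delay after an SAE or SUSAR pause, even where both physicians already agree that the event is unrelated. The length of that delay cannot be stated from the protocol. Since 5.1.5 already requires the SMC to be convened, the added burden is waiting for its ruling and not arranging an extra meeting.

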#### **5.1.2 Study Sponsor**

The sponsor (Aeras) also has an institutional responsibility to insure subject safety. This responsibility is vested in two medical monitors (one local medical monitor and one global medical monitor) and a safety monitoring committee (SMC).

#### **5.1.3 Local Medical Monitor**

The local medical monitor is the sponsor's representative and is a licensed physician or surgeon in the country of residence. The local medical monitor reviews the safety of the product for protocols in a specific region and determines expectedness of the adverse event. The local medical monitor may make a sponsor's assessment of severity and causality for adverse events that may upgrade the degree of severity and causality determined by the principal investigator. The local medical monitor, like the principal investigator, is blinded for a blinded study.

##### **5.1.3.1 Study Vaccine Pausing Rules for the Local Medical Monitor**

If the local medical monitor determines that a SUSAR OR a serious adverse event OR an adverse event pattern of concern that is judged to be POSSIBLY, PROBABLY or DEFINITELY related to study vaccine has occurred, the local medical monitor will pause administration of study vaccine in the trial. If the local medical monitor independently pauses administration of study vaccine in the study, he or she will record this in a memorandum to the study file and notify the principal investigator and sponsor who will then convene the SMC. In all cases administration of study vaccine may resume only if permitted by the SMC.

Any changes to the protocol required by the SMC as a condition of study vaccine resumption must be approved by, or submitted to, the institutional review board/ethical committee and the national regulatory authority.

#### **5.1.4 Global Medical Monitor**

A global medical monitor is retained by Aeras through the contract research organization PPD, Inc., located in Cambridge, UK. The global medical monitor reviews all SUSAR reports and since the global medical monitor is unblinded s/he determines if a report is expedited since only reports associated with an investigational agent (not placebo) are expedited. The global medical monitor may determine that the subject received placebo thus the report is entered into the database with the suspect product placebo but is not expedited and does not need to be forwarded as an expedited report. The reporting situation with active controls is different since events associated with active controls may need to be reported under post-marketing pharmacovigilance regulations.

##### **5.1.4.1 Study Vaccine Pausing Rules for the Global Medical Monitor**

Since the global medical monitor is unblinded and reviews data from all Aeras trials, he or she may become aware of an adverse event pattern of concern not appreciated by the principal investigator or local medical monitor. If the global medical monitor independently determines that an adverse event pattern of concern that is judged to be POSSIBLY, PROBABLY or DEFINITELY related to study vaccine has occurred, the global medical monitor will pause administration of study vaccine in the trial. If the global medical monitor pauses administration of study vaccine in the trial he or she will record this in a memorandum to the study file and notify the local medical monitor, principal investigator and sponsor who will convene the SMC. In all cases administration of study vaccine may resume only if permitted by the SMC. Any changes to the protocol required by the SMC as a condition of study vaccine resumption must be approved by, or submitted to, the institutional review board/ethical committee and the national regulatory authority.

#### **5.1.5 Safety Monitoring Committee**

If study vaccine administration is paused by the principal investigator, the local medical monitor, or the global medical monitor, an SMC will be convened. The SMC is composed of five voting members (two licensed physicians from South Africa, one licensed physician from the United Kingdom, and two licensed physicians from the US) and may have up to two alternate physician members. The voting members can not be directly involved with the conduct of the study, can not be employees of Aeras and must be experienced in the evaluation of adverse events in clinical trials. The SMC will also have a non-voting statistician and a non-voting Aeras member who will record committee actions.

The SMC will convene to review safety data when the last subject in the Safety Cohort (Study Group 1) completes Study Day 84. The SMC will evaluate blinded and unblinded-by-group safety data to determine if a pattern of adverse events related to MVA85A/AERAS-485 or other safety or risk concerns exist. Only the SMC and the independent statistician responsible for preparing these analyses would be unblinded during these reviews. If such a pattern

exists, the Safety Monitoring Committee will determine if additional subjects will be entered into this safety group for additional safety determination or if further studies need to be performed. The SMC will conduct a second unblinded-by-group safety and risk review after the 1000th infant completes the Study Day 84 visit. The SMC may also review an individual SAE or it may choose to review adverse events, serious adverse events, solicited adverse events, and laboratory and vital signs data. The SMC may unblind any amount of safety information needed to conduct their assessment. All procedures associated with this review, including objectives, data handling, and elements to be included for review will be documented in SMC minutes.

Based on its review and the protocol stopping rules (Section 6) the SMC will make recommendations in the SMC minutes to Aeras regarding further conduct of the study and further administration of study vaccine. The conclusions of the SMC will be communicated to the investigators and the IRB/Ethical Committees and the national regulatory authority for their information. The sponsor agrees to abide by the decision of its SMC.

#### 5.1.6 Institutional Review Boards and Ethics Committees

The Institutional Review Board or Ethics Committee has institutional responsibility for the safety of research subjects. The Institutional Review Board or Ethics Committee has the authority to terminate, suspend or require changes to a clinical trial.

#### 5.1.7 National Regulatory Authority

Since the national regulatory authority (such as the FDA for the U.S., or the MCC of South Africa) receives all expedited reports it also has the authority to terminate, suspend or require changes to a clinical trial.

### 5.2 Safety Surveillance During the Study

Subjects will be monitored and safety data collected by way of clinical interviews with parents/guardians, examinations, and evaluations of daily diaries conducted by study team members and through reports of laboratory evaluations.

Through the 28-day period following each vaccination all **adverse events** observed by the investigator (or designee) or reported by the infant's parents/guardians spontaneously in response to a direct question or recorded on the diary card, will be medically evaluated and documented in terms of a medical diagnosis on the Adverse Event CRF.

Through the entire study period all **serious adverse events** observed by the investigator (or designee) or reported by the infant's parents/guardians spontaneously or in response to a question will be medically evaluated and documented on the appropriate adverse event CRF.

